#### Physical Activity, Exercise Self-efficacy, and Mood

The responses to the structured surveys will be cleaned and analyzed using appropriate statistical methods. Data from web-based questionnaires and surveys will be classified and analyzed using Qualtrics software [65]. In addition, PASE scores will be calculated before and after experimental (exergaming) or before and after control (reading) conditions and analyzed using paired or independent 2-tailed *t* tests. Responses to the PAAS will be classified into one of the 4 affective subscales: positive affect, negative affect, physical exhaustion, and tranquility [77]. Scores within each subscale will be treated as independent outcomes to identify acute changes in affective states from before to after experimental and before to after control conditions. RPE, perceived enjoyment, exercise self-efficacy, and PAAS will be analyzed to determine potential changes over time (before vs after experimental or control conditions) and across conditions (eg, subscales and intensity).

#### Gameplay Metrics

Game metrics captured by the data logging system will be analyzed session by session, and specific metrics associated with game performance, errors, and RT will be extracted from the described variables. First, changes in SD units for each session will be determined for 3 main variables denoting game performance on each game activity: time to complete the tai chi condition, distance traveled during the rowing condition, and the number of fish caught in the fishing condition. The number of collisions will be identified as a potential variable to quantify errors during rowing. RT will be computed in the fishing condition, where the time taken by players to pull out the fishing rod after feeling the fish being hooked (controllers vibrating) will be extracted from the data files. Time will then be filtered, and values outside the 100 to 1000 ms range will be discarded [104]. All numerical data will be presented as means and SDs.

#### Exploratory Analysis

To better understand the relationship between lower-level perceptual processing and multisensory integration (assessed via the RT, SIFI, SJ, and TOJ tasks) and higher-order executive function (assessed via the modified flanker task, VF, and OTMT), exploratory correlational analyses will be conducted between the outcomes of each of the perceptual tasks (eg, TBW, point of subjective simultaneity, mean RT from the multisensory and unisensory conditions, and accuracy) and the outcomes of the modified flanker task (accuracy and mean RT), VF, and OTMT. Furthermore, exploratory analyses using correlations are planned using both game metrics and cognitive assessments (ie, modified flanker and RT tasks) for RT. Partial correlation analyses, including age, sex, and previous experience with video games as covariates, will be applied when appropriate. Correlational analyses will be conducted for outcome variables obtained before and after 6 weeks of the exergame intervention and before and after acute bouts of engagement with the exergame. The Bonferroni correction will be used to correct for multiple comparisons.

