## Methods

### Study Design

This is a 6-week pilot study to examine the feasibility, acceptability, and usefulness of a co-designed VR exergame intervention among older adults as well as the feasibility of the study procedures and assessment protocol. A control group will be used to account for practice and exposure effects and will follow the same protocol as that described for the experimental group without exposure to the exergame; they will read 3 times a week for 15 to 20 minutes instead of engaging with our exergames. To maintain consistency between the control and experimental conditions, the same questionnaires and surveys will be completed by all the participants in both groups, except for the *perceived enjoyment* and *rate of perceived exertion (RPE)* scales, which will be completed only by the experimental group. Both qualitative and quantitative methods will be used to provide pilot data on potential outcomes of interest. Although this study will evaluate the feasibility of both the study intervention and study control arms, we will not randomize the participants. Participants in the intervention arm will be recruited first, followed by a wave of participants recruited to the control group. The study is based in Waterloo but will be carried out remotely, so participants from across Canada will be eligible.

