### Statistical Analysis Plan

#### Sample Size

Given that the primary purpose of the study is to assess the feasibility and usability of at-home VR exergaming over a 6-week period, no formal sample size calculation will be performed [81]. However, to explore data collection processes and also inform sample size calculations for a larger trial, the study will aim to recruit at least 12 participants for both the experimental and control groups [82].

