#### Multisensory Integration

##### SIFI Task

Analyses will be conducted to determine whether there are differences in before and after intervention (exergaming or reading for 6 weeks) data as well as for before and after acute (1 bout of exergaming or reading) data. Analyses will be conducted separately on the proportion correct for unimodal (modality: vision-only or auditory-only) and multimodal (audiovisual conditions: nonillusory, 1 flash and 1 beep or 2 flashes and 2 beeps; or illusory, 1 flash and 2 beeps) conditions. To examine changes in susceptibility to the SIFI, sensitivity (*d*) will be calculated (*z*[hits] − *z*[false alarms]) for each SOA, and appropriate analyses will be conducted [96-98].

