## Results

This study aims for an estimated adherence rate of ≥80%. To minimize potential attrition, all participants will be provided with a thorough remote one-on-one explanation of the anticipated participation burden (time commitment) at baseline. The participants will also be contacted regularly throughout the data collection process to maintain a good working relationship and answer any questions that they may have. The participants may choose to withdraw from the study at any time and for any reason. However, they will be asked if their collected data can be used by the research team for information and data analysis purposes.

We anticipate that most of the enrolled participants will adhere to the study and follow the protocol. However, potential challenges related to nausea and motion sickness when interacting with the VR technology may lead to some dropouts in the experimental group [105-108]. Challenges related to remote assessments as well as the length and complexity of the cognitive and multisensory integration tasks may also result in attrition [109-112].

In addition, we anticipate that most participants will learn how to navigate virtual environments and successfully perform the proposed physical activities within the different stages of our exergame [113,114]. This can potentially lead to high levels of perceived enjoyment and study adherence, as found in similar studies using immersive VR with the same duration and frequency [115]. However, it is also expected that some older adults might need more support than others to set up the VR system and adapt to the technology [113,114,116,117]. These supports might need to be individualized and tailored as the pilot progresses.

Both the experimental and control conditions have been reviewed and received ethics clearance through the University of Waterloo Research Ethics Committee (experimental condition ethics clearance in April 2021 and control condition ethics clearance in June 2021). The screening and recruitment process for the experimental group started in May 2021, and the data collection process will be completed by September 2021. As of August 16, 2021, 15 community-dwelling older adults have enrolled in the experimental group, of whom 2 (13%) have dropped out. The recruitment process and data collection for the control group will start in September 2021 and be completed by December 2021.

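### As worded, the perceptual-executive correlations use exergame data alone, leaving out the reading arm (about 44-50% of participants) at a cost mainly in precision

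*Protocol article*

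**What the plan says.** The Exploratory Analysis section describes two sets of correlations.

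- **Perceptual against executive.** It states that "exploratory correlational analyses will be conducted between the outcomes of each of the perceptual tasks" (response time, sound-induced flash illusion, simultaneity judgment, temporal-order judgment) and those of the flanker, verbal fluency and Oral Trail Making tests. The stated aim is to understand how lower-level perception relates to higher-order executive function.
- **Game metrics against cognition.** It adds that "exploratory analyses using correlations are planned using both game metrics and cognitive assessments", for response time.

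A later sentence in the same section fixes the data without separating the two sets: "Correlational analyses will be conducted for outcome variables obtained before and after 6 weeks of the exergame intervention and before and after acute bouts". The acute part in full is "before and after acute bouts of engagement with the exergame". Reading does not appear anywhere in the section.

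The neighbouring analysis sections are worded differently. The SIFI Task section covers "before and after intervention (exergaming or reading for 6 weeks) data as well as for before and after acute (1 bout of exergaming or reading)" measurements. Outcome Analyses and RT Task also name exergaming and reading, and the section on physical activity, self-efficacy and mood names the experimental and control conditions.

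On the control arm, Study Design says: "A control group will be used to account for practice and exposure effects and will follow the same protocol as that described for the experimental" arm. The only instruments reserved for the experimental group there are perceived enjoyment and perceived exertion. On numbers, the Sample Size section says "the study will aim to recruit at least 12 participants for both the experimental and control groups".

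**The concern.** Readers produce no game metrics, so an exergame-only data set is unavoidable for the second set of correlations. The first set has no such reason. None of its tasks requires the game, and both arms take them on the same schedule. At baseline nobody has been exposed to either condition, so nothing in the design argues for leaving the readers out.

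An analyst who follows the sentence literally would estimate these correlations on roughly half of the available participants. In a pilot this small, that means a much wider interval around every coefficient, and a Bonferroni correction is then applied on top. After exposure, the exergamers' coefficients would also appear with no reading-arm value beside them.

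**Working it through.** The article gives no power calculation, alpha or target correlation, so there is no plan figure to reproduce. A two-sided alpha of 0.05 and bivariate normal data are assumed below. r = 0.4 is an illustrative value.

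**1. Share of participants left out**

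Inputs: at least 12 per arm (Sample Size), and from the Results section, "15 community-dwelling older adults have enrolled in the experimental group, of whom 2 (13%) have dropped out". Twelve readers are assumed throughout.

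- Planned minimum: 12/(12 + 12) = 50%.
- 13 exergamers remaining: 12/(13 + 12) = 48%.
- All 15 enrolled exergamers counted: 12/(15 + 12) = 44%.

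**2. Smallest significant |r|**

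With k variables partialled out, df = n - 2 - k and r_crit = t/√(t² + df), where t is the 97.5% point of the t distribution.

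- n = 12, k = 0: df = 10, t = 2.228, r_crit = 2.228/√(4.965 + 10) = 0.576.
- n = 24, k = 0: df = 22, t = 2.074, r_crit = 0.404.
- n = 24, arm partialled out (k = 1): df = 21, t = 2.080, r_crit = 2.080/√(4.325 + 21) = 0.413.

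Partialling out arm therefore costs about 0.01 of a gain of about 0.17.

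With the reported enrolment:

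| Exergamers | Exergamers alone | Both arms, arm partialled out |
|---|---|---|
| 12 | 0.576 | 0.413 (n = 24) |
| 13 | 0.553 | 0.404 (n = 25) |
| 15 | 0.514 | 0.388 (n = 27) |

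The gap shrinks from 0.16 to 0.15 to 0.13.

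With the section's three covariates (age, sex, video game experience), the values at the planned minimum are 0.666 for n = 12 and 0.433 for n = 24. Adding arm as a fourth covariate gives 0.444 for n = 24.

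**3. 95% interval at r = 0.4**

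Fisher z: atanh(0.4) = 0.4236, SE = 1/√(n - 3 - k), limits = tanh(0.4236 ± 1.96 × SE).

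- n = 12: SE = 1/√9 = 0.333, limits -0.23 to 0.79.
- n = 24: SE = 1/√21 = 0.218, limits 0.00 to 0.69.
- n = 24, arm partialled out: SE = 1/√20 = 0.224, limits -0.01 to 0.70.

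**4. Which pairs can be correlated at which time (Table 2)**

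- Baseline and follow-up: all four perceptual tasks and all three executive tasks.
- Acute sessions, weeks 1, 3 and 5: flanker, Oral Trail Making, verbal fluency and the RT task.
- Acute sessions, weeks 2, 4 and 6: the flash illusion task, with no executive task.
- Simultaneity and temporal-order judgment: no acute sessions.

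Within a shared acute session, only the RT task can be paired with the three executive tests, which gives 3 task pairs. The full grid of 4 × 3 = 12 task pairs exists only at baseline and follow-up.

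**5. Could a between-arm difference in correlations be tested?**

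At 12 per arm, the SE of a difference in Fisher z is √(1/9 + 1/9) = 0.471. For true correlations of 0.5 and 0, the difference is 0.549, and power is Φ(0.549/0.471 - 1.96) = 0.21. Reaching 80% power needs a z difference of 2.80 × 0.471 = 1.32, which is a correlation of about 0.87 against 0. Such a comparison can only be descriptive.

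**The case against.** The strongest reply is that no restriction is stated. The section never says that only exergamers are used, and the sentence setting out the perceptual-executive correlations names no arm. The sentence on data follows the game-metric correlations and may have been written with those in mind, or simply to list time points. This is a fair account of how the wording may have arisen. It does not change what the text fixes: that sentence speaks of correlational analyses without qualification, it is the only one in the section that sets their data, and the parallel sections do name both conditions. If the intention was narrower, the same clarification settles it.

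A reader might also infer that the exergame-only data leave practice effects uncontrolled and so bias a claim about the game. The documents do not support that. The section claims no exergame-caused link and does not specify change scores. A uniform practice gain shifts means and leaves a correlation between levels unchanged; only uneven gains would alter it. At baseline no practice comparison is needed. For the same reasons, a rule that calls a link exergame-related when the arms differ would be out of place: power is low (working, step 5), and Study Design states that the arms are not randomized and are recruited one after the other, so a difference could not be credited to the game.

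Two further points stand. Twelve per arm is a minimum, and the experimental arm has already passed it. The analysis is exploratory, in a pilot without a formal sample size calculation, and the limitations section already asks for cautious interpretation.

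**Conclusion.** The point holds as a matter of precision. Taken literally, the Exploratory Analysis section leaves the reading arm out of correlations for which that arm supplies the same data. At the planned minimum, the smallest significant |r| is 0.58 instead of about 0.41, and the 95% interval at r = 0.4 runs from -0.23 to 0.79 instead of about 0.00 to 0.69 (slightly wider with arm partialled out). With 13 to 15 exergamers the difference is somewhat smaller.

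These figures assume a two-sided alpha of 0.05, bivariate normality, 12 readers and no missing task data. The number of tests in the Bonferroni family is not stated, so thresholds after correction would be higher in both cases. No feasibility outcome and no between-group comparison of means is affected.

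**What to change.** In the Exploratory Analysis section, replace the single sentence on data with separate statements:

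1. Baseline perceptual-executive correlations: all participants of both arms, with arm partialled out.
2. Follow-up perceptual-executive correlations: name exergaming or reading, and show the correlation in each arm descriptively.
3. Acute perceptual-executive correlations: the same, limited to tasks that share sessions under Table 2, that is, the RT task with flanker, verbal fluency and Oral Trail Making.
4. State that a difference between arms in these correlations will not be attributed to the exergame.
5. Game-metric correlations: exergame group only.

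The cost is wording and one degree of freedom for arm. No participant, visit or measurement is added, because the reading arm's assessments are already scheduled.

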#### Handling of Missing Data

Any missing data will be reviewed and imputed based on the assessments that the participants complete on other days. If the missing data of a variable do not depend on the value of another variable, the analysis will be performed using both the complete data set and an analysis incorporating values from multiple imputations. If the missing data are not random, then the analysis will be completed using only the complete data set; however, differences between the 2 groups with missing and observed data will be reported.

## Results

This study aims for an estimated adherence rate of ≥80%. To minimize potential attrition, all participants will be provided with a thorough remote one-on-one explanation of the anticipated participation burden (time commitment) at baseline. The participants will also be contacted regularly throughout the data collection process to maintain a good working relationship and answer any questions that they may have. The participants may choose to withdraw from the study at any time and for any reason. However, they will be asked if their collected data can be used by the research team for information and data analysis purposes.

We anticipate that most of the enrolled participants will adhere to the study and follow the protocol. However, potential challenges related to nausea and motion sickness when interacting with the VR technology may lead to some dropouts in the experimental group [105-108]. Challenges related to remote assessments as well as the length and complexity of the cognitive and multisensory integration tasks may also result in attrition [109-112].

In addition, we anticipate that most participants will learn how to navigate virtual environments and successfully perform the proposed physical activities within the different stages of our exergame [113,114]. This can potentially lead to high levels of perceived enjoyment and study adherence, as found in similar studies using immersive VR with the same duration and frequency [115]. However, it is also expected that some older adults might need more support than others to set up the VR system and adapt to the technology [113,114,116,117]. These supports might need to be individualized and tailored as the pilot progresses.

Both the experimental and control conditions have been reviewed and received ethics clearance through the University of Waterloo Research Ethics Committee (experimental condition ethics clearance in April 2021 and control condition ethics clearance in June 2021). The screening and recruitment process for the experimental group started in May 2021, and the data collection process will be completed by September 2021. As of August 16, 2021, 15 community-dwelling older adults have enrolled in the experimental group, of whom 2 (13%) have dropped out. The recruitment process and data collection for the control group will start in September 2021 and be completed by December 2021.

## Discussion

### Overview

The use of immersive VR for promoting exercise among older adults is an emerging field of research with special relevance because of the COVID-19 pandemic. Social distancing measures and the closure of exercise facilities have been creating a more demanding need for effective home-based programs to encourage physical activity participation and enhance older adults’ well-being. This pilot study is a result of the need to move to remote research following pandemic restrictions and rapid technological advancements and adoption.

This study aims to assess the feasibility of exploring changes in perceived levels of physical activity, exercise self-efficacy, mood, executive function, and multisensory integration. Although some studies have been validated for at-home remote administration [47,52], this approach is still not commonly used and has not yet been used in conjunction with VR exergames. Challenges related to remote research, unstable internet connection, monotony with regard to multiple sessions, computer use, human errors, and eye strain are expected during remote testing [110,111,118-120]; part of this pilot is to hone ways to mitigate and solve these challenges remotely. This pilot will add insights into the feasibility of implementing a relatively complex, remotely administered assessment protocol for older adults living at home.

This protocol also addresses unexplored research questions regarding the use of state-of-the-art VR technologies and custom-made exergames tailored to older adults for home-based programs. First, this study will examine the feasibility of deploying exercise programs using immersive VR with *Seas The Day* during the COVID-19 pandemic. The study intervention has a longer duration than the average found in similar studies of the same nature [47,52]. Other studies using immersive VR in older adults have exposed participants to VR experiences ranging from 1 to 55 minutes, with 15 minutes being the most common exposure time [47,121,122]. Although many elements are included in this study to support community-dwelling older adults to easily set up and use the VR system at home, challenges associated with system calibration, the overall use of the tracking system, and potential motion sickness, among others, are to be expected during the study [105-108,113,114].

The deployment of VR systems at home also has the novel potential to capture data during gameplay, which may be able to capture changes not only in game performance but also in older adults’ well-being. In this study, the VR system will capture a broad range of variables that will be used to recreate the microinteractions and behaviors of the participants during their interaction with *Seas The Day.* Although exploratory, previous work has shown how gameplay metrics have the potential to be powerful descriptors of elements related to physical and cognitive functioning, which are very important aspects when tracking the progress and benefits of exercise programs [121,122].

### Strengths and Limitations

This study will establish the feasibility of deploying a VR system to older adults across Canada for health application purposes. This study will also assess the feasibility of a complex assessment protocol. Both may provide useful insights for the future of remote, virtual research and are specific not only to VR research but also more broadly applicable.

Reaching our target population may be challenging during the COVID-19 pandemic and will likely be restricted to older adults who are open to the use of technology and have the ability to do so (eg, have a computer or tablet and internet already). In addition, older adults may be hesitant to participate because of (1) technology apprehension, (2) availability of other physical activity options (as, at the time this paper was written, the restrictions had started to loosen up), and (3) time commitment (8 weeks total, with multiple tests and web-based meetings). We plan to minimize the impact of these limitations by carrying out introductory sessions to facilitate the usability of the technology at the beginning of the trial, using stand-alone VR systems that are portable and can be used without an internet connection, and building rapport with all the participants to facilitate a long-standing research relationship and reduce the burden of taking part in this research remotely.

Another important limitation associated with this pilot study protocol is a lack of control over the VR exergame and assessment environment. Although we will strongly suggest that the participants engage with the exergames in the mornings and preferably on the same days every week, we cannot ensure that these guidelines will be followed. Unlike tasks administered in a well-controlled laboratory environment, the cognitive and perceptual tasks will be administered to the participants in the comfort of their homes through a web-based platform, which reduces our control over the size, brightness, and intensity of the stimuli. Furthermore, variations in the size and positioning of the monitor and keyboard as well as the placement of the speakers further decrease experimental control. The participants will be encouraged to maintain their environment (eg, use the same monitor and stay in the same room) once they complete their first session of cognitive and perceptual tasks, establishing consistency within the participants. Although these challenges may make collecting data more difficult, they also represent data that are much closer to real-world everyday use than they would be in a laboratory environment.

Finally, the small sample size of this pilot study and the disadvantages associated with self-reported questionnaires (eg, inaccurate data and social desirability bias) limit the generalizability of the results and, thus, the statistical analyses must be interpreted with caution [123,124].

